**Methods:**

We will conduct a randomized, double-blind, sham-controlled trial involving 175 participants aged 20–55 years, stratified by food addiction status (FA+ vs. FA-) using the Yale Food Addiction Scale (YFAS 2.0). Participants will receive tACS at alpha (10 Hz) or theta (6 Hz) frequency over the DLPFC, ACC, or insula for seven consecutive days. Electroencephalography (EEG) and functional magnetic resonance imaging (fMRI) will be conducted pre- and post-intervention. Primary outcomes include changes in craving intensity and inhibitory control. Secondary outcomes include alterations in neural oscillations and functional connectivity.

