## 2 Methods

### 2.1 Study design

This randomized, double-blind, sham-controlled, parallel-group trial is designed to investigate the effects of fixed-frequency transcranial alternating current stimulation (tACS) on food cravings, inhibitory control, and associated neural oscillations. The study includes participants with and without food addiction, classified according to the Yale Food Addiction Scale 2.0 (YFAS 2.0).

Participants classified as food-addicted (FA+) will be randomly assigned to one of four intervention arms: (1) active tACS targeting the anterior cingulate cortex (ACC) at a theta frequency of 6 Hz, (2) active tACS targeting the dorsolateral prefrontal cortex (DLPFC) at an alpha frequency of 10 Hz, (3) active tACS targeting the insula at a theta frequency of 6 Hz, or (4) sham tACS serving as a placebo control.

Participants classified as non-addicted (FA-) will be assigned to a separate fifth group. This group will follow a within-subject, counterbalanced crossover design in which each participant receives both active and sham stimulation across two sessions. Sessions will be scheduled on consecutive days, with a 24-h interval, and the stimulation order randomized to mitigate order effects. This approach enables within-subject comparison of stimulation effects in individuals without food addiction and allows for additional between-group analyses contrasting FA+ and FA- responses. Furthermore, the crossover approach in the FA- group is selected to reduce unnecessary stimulation exposure and focus statistical power on the primary FA+ comparisons, while still enabling exploratory within-subject analyses in non-addicted participants.

This design allows for direct comparisons between active and sham conditions and across cortical targets while also enabling exploration of craving-related network dynamics in the presence and absence of FA.

Randomization will be conducted using a computerized block randomization algorithm, stratified by food addiction status (FA+ vs. FA-). To ensure allocation concealment, the randomization sequence will be generated by a researcher not involved in data collection or analysis. All participants, tACS administrators, and outcome assessors will remain blind to group allocation throughout the study.

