Data management will be conducted in accordance with ethical data protection standards. All data will be stored on a secure, encrypted server with access limited to authorized personnel. Personal identifiers will be removed and replaced with anonymized participant codes. Missing data will be handled using multiple imputations via chained equations (MICE), assuming data are missing at random. Sensitivity analyses will be conducted to test the robustness of findings under different imputation models.

All statistical analyses will follow an intention-to-treat approach. The primary outcome–change in S-FCQ and FCI scores–will be analyzed using repeated measures ANOVA, with time (pre/post) and group (stimulation target and sham) as factors. *Post hoc* comparisons will be corrected using the Bonferroni method. Changes in Go/No-Go performance will be analyzed using ANCOVA, adjusting baseline reaction times and error rates. EEG parameters will be analyzed using linear mixed-effects models to account for within-subject correlations across sessions. Functional connectivity changes in fMRI will be assessed using seed-based and ICA models, with between-group comparisons conducted using *t*-tests or mixed models where appropriate. Longitudinal changes in YFAS and T-FCQ scores will be modeled using hierarchical linear regression.

Exploratory analyses will examine whether individual differences in sex, BMI, and baseline craving severity moderate the effects of tACS. Clustering methods will also be used to identify subgroups based on EEG and fMRI response profiles.

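### Food addiction status, the only stratification factor named, is constant among the 140 participants randomised to the four arms, so it balances nothing in the primary comparison

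*Protocol article*

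**What the plan says.** Section 2.1 of the protocol article sets out the allocation in three statements:

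- "Participants classified as food-addicted (FA+) will be randomly assigned to one of four intervention arms": ACC, DLPFC, insula or sham.
- "Participants classified as non-addicted (FA-) will be assigned to a separate fifth group". That group is a crossover, with "the stimulation order randomized to mitigate order effects".
- Randomisation uses a "computerized block randomization algorithm, stratified by food addiction status (FA+ vs. FA"-). No other stratification factor is given.

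Section 2.2.5 puts 140 participants in the FA+ parallel groups and 35 in the FA- crossover. Section 2.1 explains that the crossover was chosen partly to "focus statistical power on the primary FA+ comparisons". Section 2.5 analyses the craving outcomes by repeated-measures ANOVA "with time (pre/post) and group (stimulation target and sham) as factors". The abstract describes a randomised trial of "175 participants aged 20–55 years, stratified by food addiction status (FA+ vs. FA"-).

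Section 2.5 also plans exploratory analyses of whether "individual differences in sex, BMI, and baseline craving severity moderate the effects of tACS". According to section 2.2.3, BMI, craving intensity and YFAS 2.0 are all collected at the online prescreen.

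**The concern.** A stratification factor does its work by taking more than one value among the people being randomised. Here food addiction status decides which randomisation a person enters, and within the four-arm randomisation it has a single value. The stated scheme therefore gives no protection against chance differences between an active arm and sham at 35 per arm. Characteristics that do vary within FA+ and that the protocol itself considers relevant (sex, BMI, baseline craving, YFAS severity) are not used.

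Precision and credibility of the active-versus-sham comparisons are at stake; validity is not. There is also a question of description: a reader of the abstract alone could think that 175 people are allocated to treatment arms with food addiction status balanced across them.

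**Working it through.** **1. The plan's own numbers.** 4 × 35 = 140 FA+, plus 1 × 35 FA-, gives 175. This reproduces section 2.2.5.

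**2. Stratum by group, from the rules in section 2.1 (equal arms).**

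| | ACC | DLPFC | Insula | Sham | Fifth group |
|---|---|---|---|---|---|
| FA+ | 35 | 35 | 35 | 35 | 0 |
| FA- | 0 | 0 | 0 | 0 | 35 |

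Within the four randomised arms the factor has one level (140 of 140 FA+). As a check, a permuted-block sequence for 140 participants was generated twice from the same seed, with and without the food addiction factor (block size 4 assumed, since none is stated). The two sequences were identical.

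**3. Size of chance imbalance without effective strata.** For a continuous baseline variable in SD units, the difference between one active arm and sham has standard error √(1/35 + 1/35) = √(2/35) = 0.239.

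- More than 0.25 SD in one comparison: 0.25/0.239 = 1.05, two-sided probability about 0.30.
- More than 0.40 SD in one comparison: 0.40/0.239 = 1.67, probability about 0.09.
- In at least one of three comparisons, if they were independent: 1 − 0.70³ = 0.66 and 1 − 0.91³ = 0.25. The three share one sham arm, which lowers these. Simulation gives about 59% and 22–23%.

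**4. What strata that vary within FA+ would change.** Simulation of 140 participants in blocks of 4. Assumptions, none of them given in the document: 30% men, YFAS score treated as continuous and split at the median, craving–YFAS correlation 0.3. The entries are the chance that at least one active arm differs from sham by the stated amount.

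| Baseline factor | Unstratified | Stratified by sex and YFAS band |
|---|---|---|
| YFAS, more than 0.25 SD | about 58% | about 21% |
| Sex, 20 points or more | about 20% | 0% |
| Craving, more than 0.25 SD | about 59% | about 57% |

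At assumed craving–YFAS correlations of 0 and 0.5, the stratified craving figure is about 60% and 54%. These strata therefore leave craving imbalance essentially as it was.

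**5. Why craving needs adjustment.** With two time points, the group-by-time term in the craving ANOVA compares change scores. If an arm starts d SD above sham and the pre–post correlation is r (equal variances), the expected difference in change is −(1 − r)d with no treatment effect. At d = 0.25 and an assumed r of 0.5 this is −0.5 × 0.25 = −0.125 SD. It averages to zero over randomisations, and baseline adjustment removes it.

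**The case against.** The strongest reply is that nothing is wrong. Stratified by food addiction status can be read as one list per status, four arms for FA+ and session order for FA-, which is workable and harmless. Unstratified blocking is a valid design, and chance imbalance is random error that the test already allows for. The percentages above would apply to any trial of four arms of 35 without covariate strata, and the 0.25 SD and 20-point thresholds are arbitrary. Section 2.5 brings in each outcome's own baseline, through the pre/post factor for craving and through ANCOVA for Go/No-Go. The moderator analyses are exploratory and do not oblige anyone to stratify.

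Most of this stands. The two-list reading is the only workable one, and on it the FA+ list has no stratification factor, which the text does not say. The model argument holds for each outcome's own baseline, only partly for craving (step 5), and not for sex or YFAS severity, which section 2.5 does not name as covariates in the primary models.

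A reader might infer more than the document supports. It does not follow that the primary comparison is biased or its type I error inflated. Nor does the protocol assert that sex, BMI and craving modify the effect; it will explore whether they do. The abstract is loosely worded, but it can be read as classifying the sample by YFAS, and section 2.1 separates random assignment of FA+ participants from placement of FA- participants. It does not claim that FA+ versus FA- is randomised.

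**Conclusion.** The point holds as a wasted stratification, of low to moderate severity. The one named factor is constant across all 140 participants in the primary comparison, so their allocation is blocked but unstratified. This part rests on section 2.1 alone and needs no assumption.

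The gain from better strata is real but limited: about 58% to 21% for YFAS imbalance and about 20% to 0% for sex imbalance, under the assumed 30% men, median split and blocks of 4. It would be wrong to infer that these strata also repair baseline craving. They do not, and that has to be handled in the analysis.

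**What to change.** Before enrolment, which per section 4 still awaits final ethics approval and registration:

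1. In section 2.1, describe two randomisation lists. For the 140 FA+ participants, use four-arm block randomisation stratified by factors that vary within FA+ and are known at screening, for example sex and a YFAS 2.0 severity band with its cut-off fixed in advance. For the 35 FA- participants, randomise session order only.
2. In section 2.5, include the chosen stratification factors as covariates in the primary models, and adjust the craving analysis for baseline craving.
3. In the abstract and section 2.1, state that 140 participants are randomised to arms and that FA+ versus FA- is a non-randomised comparison.

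If the sponsor prefers no strata, the minimum is to say that the FA+ list is blocked and unstratified, and still to make changes 2 (baseline craving) and 3.

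The cost is a revised computer-generated list and a few sentences; no extra data are needed. The downside is four strata instead of one, each of which may end in an incomplete block. With blocks of 4, two arms can differ by at most 1 within a stratum, so by at most 4 × 1 = 4 overall. Once the first participant is allocated, the list can no longer be changed cleanly.

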### 2.2 Participants

#### 2.2.1 Eligibility criteria

Participants will be adults between the ages of 20 and 55 years with a Body Mass Index (BMI) of 18.5 or higher. All participants must report high levels of food cravings and demonstrate English language proficiency sufficient to complete study procedures. To ensure physiological stability, individuals must have maintained a body weight within ± 5% of their average over the past 3 months.

Food addiction status will be assessed using the YFAS 2.0. Participants with a YFAS 2.0 score ≤ 1 will be classified as non-addicted (FA-), while those scoring ≥ 2 will be classified as food-addicted (FA+), following validated cutoff recommendations (Gearhardt et al., 2016).

#### 2.2.2 Exclusion criteria

Participants will be excluded if they have any contraindications to tACS or magnetic resonance imaging (MRI), including implanted electronic devices, metal implants in the head, or a history of seizures. Individuals with current or past diagnoses of neurological or psychiatric disorders (e.g., epilepsy, major depression, bipolar disorder, schizophrenia), as well as those meeting the DSM-5 criteria for a SUD, will be excluded. The use of medications that may influence neural connectivity or craving regulation, including psychoactive agents, appetite suppressants, and hormonal therapies, will also result in exclusion.

Additional exclusion criteria include participation in structured weight-loss programs; chronic medical conditions affecting metabolism (e.g., diabetes, thyroid dysfunction, renal disease, autoimmune disorders); and pregnancy, breastfeeding, or postmenopausal status. These exclusions aim to minimize confounding variables and ensure participant safety.

#### 2.2.3 Recruitment and screening

Participants will be recruited through university mailing lists, social media platforms, and targeted community outreach efforts. Interested individuals will first complete an online prescreening survey assessing basic eligibility, including age, BMI, craving intensity, and food addiction status using the YFAS 2.0.

Those meeting the initial criteria will be invited for an in-person screening, during which eligibility will be confirmed through structured interviews and validated behavioral assessments. These will include the State Food Craving Questionnaire (S-FCQ), Trait Food Craving Questionnaire (T-FCQ), Food Craving Inventory (FCI), and the Center for Epidemiologic Studies Depression Scale – Revised (CESD-R). The CESD-R will be used to rule out significant depressive symptoms that could influence craving or intervention response.

#### 2.2.4 Ethical approval and informed consent

Written informed consent will be obtained from all participants prior to enrollment. The study will be conducted in accordance with the Declaration of Helsinki and has been submitted for approval to both the Abu Dhabi Health Research and Technology Committee (ADHRTC) and the United Arab Emirates University Human Research Ethics Committee (UAEU-HREC).

#### 2.2.5 Sample size and power considerations

The sample size was calculated based on prior studies investigating neuromodulation effects on craving-related behavior and oscillatory activity (Song et al., 2019, 2022; Althubaiti, 2022; Kim et al., 2023; Gairola et al., 2024; Arifin and Yaacob, 2025; Sánchez-Garrido Campos et al., 2025). Assuming a moderate effect size (Cohen’s f = 0.25), an alpha level of 0.05, and a desired power of 0.80, a minimum of 35 participants per group is required to detect statistically significant differences in the primary behavioral outcome.

To account for potential attrition and non-compliance, a 20% dropout rate was incorporated into the calculation, yielding a final target of 175 participants distributed across the five study groups. This includes 140 participants in the FA+ parallel groups and 35 in the FA- crossover group.

Given the multimodal nature of data collection, including repeated electroencephalography (EEG) and functional magnetic resonance imaging (fMRI) measurements, a sensitivity analysis was also conducted. This analysis confirmed that the study remains adequately powered to detect within-subject changes in neural and behavioral outcomes while maintaining sufficient statistical power for between-group comparisons.

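### Section 2.2.5 gives 35 per group both as the minimum required for 80% power and as the size after a 20% dropout allowance; both cannot be true

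*Protocol article*

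**What the plan says.** The protocol article, Section 2.2.5, makes three statements in sequence.

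- With f = 0.25, "an alpha level of 0.05, and a desired power of 0.80", it says that "a minimum of 35 participants per group is required to detect statistically significant differences in the primary behavioral outcome".
- For attrition and non-compliance, "a 20% dropout rate was incorporated into the calculation, yielding a final target of 175 participants distributed across the five study groups".
- The total is then split: "This includes 140 participants in the FA+ parallel groups and 35 in the FA- crossover group".

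Section 2.1 says that FA+ participants "will be randomly assigned to one of four intervention arms". It places FA- participants in a separate two-session crossover, chosen partly so that power is concentrated on the FA+ comparisons. Section 2.5 says that the craving outcomes "will be analyzed using repeated measures ANOVA, with time (pre/post) and group (stimulation target and sham) as factors", and that Go/No-Go performance will be analysed by ANCOVA. No other section gives a separate evaluable number.

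**The concern.** A number required for 80% power and a number enrolled after allowing for 20% loss should differ by that loss. Here both are 35 per group. Either the allowance was never added, or the figure called the minimum already contains it. A reader, ethics committee or funder is told that 80% power survives 20% attrition. If the first explanation is right, it does not, and a null result would be given more weight than it deserves.

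The total is also spread over five groups, although only four are arms of the randomised parallel comparison. The FA- group has a different design and cannot serve as a fifth arm in a power calculation for that comparison.

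**Working it through.** **Inputs.** Section 2.2.5: f = 0.25, alpha 0.05, power 0.80, 35 per group, 20% dropout, total 175 (140 FA+ and 35 FA-). Section 2.1: four FA+ arms. Not stated: the test behind 35, the number of measurements m and the correlation ρ between them. The values of m and ρ below are assumptions.

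**Step 1: the plan's totals.** 5 × 35 = 175 and 4 × 35 = 140. Both reproduce with no dropout allowance added.

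**Step 2: the allowance.**
- Dividing by the retained fraction: 35 / 0.80 = 43.75, so 44 per group; 4 × 44 = 176 FA+ and 5 × 44 = 220 in all.
- The cruder multiplication: 35 × 1.2 = 42 per group, 210 in all.
- Neither gives 175. Working back, 35 × 0.80 = 28 evaluable per group, and 4 × 28 = 112 FA+.

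**Step 3: taking 35 as the true minimum.** If the effect is set so that 35 per group gives exactly 80% in a one-way F test, f is 0.283 with four groups and 0.265 with five. Power at 28 is then 0.69 in both cases. This needs no assumption about ρ.

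**Step 4: power at f = 0.25, four FA+ arms.** Noncentral F, alpha 0.05, N = 4n, so N f² = 112 × 0.0625 = 7.0 at n = 28 and 140 × 0.0625 = 8.75 at n = 35.

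| Calculation | Noncentrality | Value at n = 28 | n needed per arm | Power at 35 | Power at 28 |
|---|---|---|---|---|---|
| One-way test on change, f on the change score | N f² | 7.0 | 45 | 0.68 | 0.57 |
| ANCOVA, ρ = 0.5 | N f² / (1 − ρ²) | 7.0 / 0.75 = 9.33 | 34 | 0.82 | 0.71 |
| Repeated-measures between factor, m = 2, ρ = 0.5 | N f² m / (1 + (m − 1)ρ) | 14 / 1.5 = 9.33 | 34 | 0.82 | 0.71 |
| Time × group, usual software convention, m = 2, ρ = 0 | N f² m / (1 − ρ) | 14 | 23 | 0.95 | 0.88 |
| The same, ρ = 0.5 | as above | 14 / 0.5 = 28 | 12 | above 0.99 | above 0.99 |

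**Step 5: can 28 be the required number?** 28 / 0.80 = 35 exactly. A repeated-measures between factor with four groups and ρ = 0.5 needs 29 per arm with four measurements (power 0.80 at 28) and 28 with five (0.81 at 28). ANCOVA with ρ = 0.6 needs 29. So a requirement near 28, inflated to 35, is possible, but the text does not say so.

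**The case against.** The strongest reply is that the dropout sentence describes the allowance as already part of the calculation, so 35 may be 28 inflated. Step 5 shows that this is arithmetically possible, and it stands as one reading. It moves the error without removing it: the sentence calling 35 the minimum required would then be false.

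A reader might infer that the trial simply lacks 80% power, perhaps quoting 0.57. The document does not support so flat a claim. The 0.57 belongs to a one-way test on change with f defined on the change score. Section 2.5 names repeated measures ANOVA for craving and ANCOVA for Go/No-Go, and Section 2.2.5 does not say to which scale f refers. With f = 0.25 placed on the time × group interaction, 28 per arm gives 0.88 or more. That convention needs only 8 to 23 per arm for ρ from 0.7 down to 0, so it does not make 35 the minimum either.

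A reader might also infer that 35 cannot come from the stated inputs. It nearly does: ANCOVA, or a repeated-measures between factor with two measurements, gives 34 at ρ = 0.5. An article may leave the correlation to a fuller document. For the same reason, the absence of figures for the sensitivity analysis is not faulted here. Nor is power for the Bonferroni-corrected post hoc contrasts, since Section 2.2.5 claims none.

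The plan for missing data does not resolve the matter. Section 2.5 states: "Missing data will be handled using multiple imputations via chained equations (MICE), assuming data are missing at random". Imputation handles missing values under that assumption, but it does not restore the information that dropouts would have supplied.

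**Conclusion.** The contradiction is certain and rests on no modelling assumption: no reading makes both the minimum and the dropout allowance true.

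The consequence for power is conditional. If 35 evaluable is the minimum, as the text says, 20% dropout leaves 28 per arm and power of about 0.69 to 0.71, roughly ten points below the stated 0.80. The lower value is calibrated to exactly 80% at 35; the upper is the ρ = 0.5 case, which starts from 0.82. If 28 was the requirement, the power claim may stand and the wording of the minimum is wrong. Which applies cannot be settled from the document, because the test, the number of measurements and the correlation behind 35 are not given.

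**What to change.** Revise Section 2.2.5 without changing enrolment:

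- State the number randomised per FA+ arm (35) and the number expected to be evaluable after 20% dropout (about 28) separately, and say which of the two the calculation required.
- Restate the power, or the detectable effect, at 28 per arm for the four-arm FA+ comparison under the planned analysis. Name the test, the number of measurements, the assumed correlation and the scale on which f is defined.
- Report the FA- crossover group separately, and not as a fifth arm of that calculation.

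The cost is the rewording of one section. The downside is that the stated power may become less favourable. Section 4 places final ethics approval and registration before enrolment, so the correction can precede recruitment if that stage has not passed.

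### One 20% dropout rate is meant to cover both attrition and non-compliance, but it cannot offset dilution under intention-to-treat, and the target of 35 per group contains no allowance at all

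*Protocol article*

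**What the plan says.** Section 2.2.5 sets out the inputs: "Assuming a moderate effect size (Cohen’s f = 0.25), an alpha level of 0.05, and a desired power of 0.80". From these it concludes that "a minimum of 35 participants per group is required to detect statistically significant differences in the primary behavioral outcome". It then adds: "To account for potential attrition and non-compliance, a 20% dropout rate was incorporated into the calculation". The outcome of that step is described as "yielding a final target of 175 participants distributed across the five study groups". The allocation follows: "This includes 140 participants in the FA+ parallel groups and 35 in the FA- crossover group".

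Section 2.5 fixes the analysis population: "All statistical analyses will follow an intention-to-treat approach". The same section handles missing data by multiple imputation under missing at random, and analyses the craving scores by a repeated measures ANOVA with time and group as factors.

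The article does not split the 20%, define non-compliance, or say whether f = 0.25 is expected in everyone randomised or only in those who receive the full course.

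**The concern.** Attrition and non-compliance act on power in different ways. A participant who leaves takes information away, and enrolling 1/(1-d) times as many replaces it. A participant who stays but misses stimulation is, under intention-to-treat, still analysed in the assigned arm. The sample does not shrink, but the average effect may. If a share c has no effect, f becomes f(1-c), and the enrolment factor is 1/(1-c)² instead of 1/(1-c). Section 2.2.5 counts both events as losses, which does not fit the analysis rule in section 2.5.

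The allowance is also not visible in the target. Five groups at the stated minimum of 35 already make 175.

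At stake is how a null result would be read. If the trial is described as having 80% power for a moderate effect when its power is lower, a non-significant result could be taken as stronger evidence against that effect than it is.

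**Working it through.** **Inputs from section 2.2.5.** f = 0.25, alpha 0.05, power 0.80, minimum 35 per group, pooled allowance 20%, target 175 = 140 + 35. The comparison examined is the one among the four FA+ arms (4 × 35 = 140), because the FA- group follows a separate crossover.

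**Assumptions, not in the article.** Correlation between repeated measures r = 0.5 where needed; non-compliance between 0 and 20% within the 20%; no effect, or half the effect, in non-compliers; attrition treated as lost information.

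**Step 1: reproduce the minimum.** For f = 0.25 and 80% power, a noncentral F calculation gives the following for four groups:

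| Test | n per group |
|---|---|
| One-way ANOVA | 45 |
| Repeated measures, between-group test, 2 measures, r = 0.5 | 34 |
| ANCOVA, r = 0.5 | 34 |
| Time × group interaction, 2 measures, r = 0.5 | 12 |

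So 35 is reproduced only approximately, under variants the article does not name.

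**Step 2: reproduce the target.** 35/(1 - 0.20) = 43.75, so 44 per group and 5 × 44 = 220 in total. The less exact 35 × 1.20 = 42 gives 210. Neither is 175. A target of 35 would contain a 20% allowance only if the minimum were 28 (28/0.8 = 35), which contradicts the stated 35.

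**Step 3: calibrate.** Take the article at its word that 35 analysed per arm gives 80%. With 4 arms, N = 140 and df 3 and 136, the noncentrality giving 80% power is 11.22. The implied effect size is √(11.22/140) = 0.283. This is not the stated 0.25: in a plain one-way model f = 0.25 at 35 per arm gives only 68%, before any loss. The calibration gives the plan its own 80% and measures departures from it.

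**Step 4: power at 35 enrolled per arm.** Noncentrality = 11.22 × (1 - attrition) × (1 - dilution)², where dilution is the non-compliant share times the share of effect lost.

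| Scenario | Noncentrality | Power |
|---|---|---|
| 20% attrition | 11.22 × 0.80 = 8.98 | 69% |
| 10% attrition, 10% non-compliance, no effect | 11.22 × 0.90 × 0.81 = 8.18 | 65% |
| 20% non-compliance, no effect (worst case) | 11.22 × 0.64 = 7.18 | 59% |
| 20% non-compliance, half the effect kept | 11.22 × 0.90² = 9.09 | 70% |

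**Step 5: would a correct 20% inflation repair it?** At 44 per arm the first three scenarios give 80%, 76% and 70%; the half-effect scenario gives about 81%. Reading the plan as 28 needed and 35 enrolled gives the same 80%, 76% and 70% in the first three. The factors needed for 80% in those three are 1/0.80 = 1.25, 1/(0.90 × 0.81) = 1.37 and 1/0.64 = 1.56.

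**The case against.** The strongest objection concerns what f = 0.25 means. A reader might infer that it is an effect in full compliers, so that a dilution correction is certainly due. The article does not say so. It refers to prior studies, and if f already describes everyone randomised, no reduction is needed for non-compliance. That stands. Even so, non-compliance would then not belong in a dropout rate either.

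Second, a retained participant with no effect fits this trial only in part. Section 2.4 places the primary measurements immediately before and after the sessions on Days 1 and 5. Someone with a post-session score normally attended that session, and a missed Day 5 session usually means missing data, which is imputed and costs information instead of diluting the effect. Sessions missed in between cannot affect the Day 1 contrast and only partly affect Day 5. Dilution remains possible for cumulative change and for Day 8. The 59% figure is therefore a worst case.

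Third, a reader might infer from seven consecutive daily sessions that missed sessions are likely. The article gives no rate to support that; it shows only that some non-compliance was anticipated.

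Fourth, the percentages depend on the model. If f = 0.25 referred to the time × group interaction with r = 0.5, power at 35 per arm would stay near 98% even with 20% dilution. That variant needs only 12 per group, however, so it does not explain the stated 35.

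Finally, dilution is the smaller of the two problems. Attrition alone already brings power to 69% at 35 per arm, and the half-effect case is no worse than that.

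**Conclusion.** The point holds in a limited form. The article pools two events that need different allowances, its intention-to-treat rule makes the pooling inappropriate, and the target does not contain the allowance in any case. The stated 80% is therefore not secured on the plan's own figures.

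The missing inflation is the main loss, from 80% to about 69% at 35 per arm. Full dilution removes up to about 10 points more (69% to 59%), and about 4 in the 10/10 split. The errors are separate: repairing only the inflation restores 80% under pure attrition but leaves 70% to 76% in the two zero-effect scenarios.

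These figures rest on 35 analysed per arm being the 80% size, on four FA+ arms, on an implied f of about 0.28, and on assumed splits and effects in non-compliers. A reader might infer that the trial's true power is 59%, or that dilution of a known size has been shown. The documents support neither, since they give no split, no rate and no definition of the effect to which f = 0.25 refers.

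**What to change.** Revise section 2.2.5 as follows.

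1. State the test, the number of groups and the correlation behind 35 per group, and whether f = 0.25 is an intention-to-treat or a full-compliance effect.
2. Separate the 20% into attrition and non-compliance, and define the latter.
3. Allow for attrition by 1/(1-d). Allow for non-compliance by a reduced f, and only if f is a full-compliance effect.
4. Replace the 80% by the power, or the detectable f, that applies at the planned 35 per arm, with a range across plausible splits. On the calibration used here, 20% attrition leaves 28 analysed per arm and a detectable f of about 0.32, against 0.28 with no loss.

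The cost is one revised paragraph and a less favourable power statement. No more participants are required if the sponsor accepts the restated power. A supplementary adherence analysis, for example with randomised arm as an instrument for sessions received, is optional and not part of the correction.
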